### Economic evaluation

Direct medical costs, non-medical costs and time-cost differences will be calculated for each arm of the study. These will include the increased costs in the PRECious arm due to the extra CRP testing and greater use of CT, and costs due to complications and readmissions. We expect admission duration to be shorter in the PRECious arm due to early diagnosis and treatment of complications. Therefore, the protocol committee deems the protocol cost-effective. On retrospective analysis of direct medical costs in patients who underwent MAS the average cost was 8.584,81 € (95 % CI 8.332,51 − 8.860,81 €) in patients without complications, 15.412,96 € (95 % CI 14.250,22 − 16.708,82 €) after minor complications, and 29.198,23 € (95 % CI 27.187,13 − 31.295, 78 €) in patients with a major complication that required invasive treatment (*p* <0.001) [5].

### Ethics

The study will be conducted in accordance with the principles of the Declaration of Helsinki and Good Clinical Practice guidelines. The protocol has been written in concordance with the SPIRIT guidelines, as depicted in the checklist (see Additional file 1) [40]. The scientific research committee of the Cancer Center Amsterdam, the Netherlands, approved the study on 12 March 2014 (ID: Pro 14/23). Approval by the medical ethics committee of the VU University Medical Center, Amsterdam was obtained on 26 May 2015 (Protocol ID 2015.114 – NL43534.029.15). The board of executives in each participating center will have to approve the final protocol (version 2.0, 4 May 2015) prior to the start of inclusions. Written informed consent will be obtained from all participating patients. This trial was registered at clinicaltrials.gov on 5 February 2015, with trial number NCT02102217.

### Postoperative quality control

#### Preoperative preparation

Patients in both groups will receive similar preoperative treatment. Standard anti-thrombotic prophylaxis will be administered according to the local protocol. Furthermore, standard prophylactic antibiotics will be administered according to the local protocol.

#### Standard group

In the first period all patients will be allocated to the control group and will receive standard postoperative monitoring, which consists of daily measurement of clinical parameters (heart rate, blood pressure, temperature, pain) and assessment of the patient by the attending physician. Additional examinations such as blood sampling and imaging will only be conducted on demand, for instance, if clinical parameters deviate or physical examination shows signs of complications.

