**Methods:**

A multicenter, stepped wedge, prospective clinical trial including all adult patients planned to undergo elective MAS. The first period consists of standard postoperative monitoring, which entails on demand additional examinations. This is followed by a period with implementation of postoperative control according to the PRECious protocol, which implicates standardized measurement of CRP levels. If CRP levels exceed 140 mg/L on postoperative day 3,4 or 5, an enhanced CT-scan is performed.

Primary outcome in this study is a combined primary outcome, entailing all morbidity and mortality due to postoperative complications. Complications are graded according to the Clavien-Dindo classification. Secondary outcomes are hospital length of stay, patients reported outcome measures (PROMs) and cost-effectiveness. Data will be collected during admission, three months and one year postoperatively. Approval by the medical ethics committee of the VU University Medical Center was obtained (ID 2015.114).

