In 2008, Den Dulk et al. implemented a standardized scoring system for the clinical status of patients undergoing colorectal surgery. With this system they decreased the time between surgery and diagnosis of anastomotic leakage from 8 to 6 days, thereby decreasing mortality from 39 % to 24 % (*p* = 0,24), further supporting the role of a standardized postoperative quality control algorithm following MAS [6, 7]. However the search for an optimal algorithm continues. CRP and CT scanning have been shown to differentiate between an uncomplicated and a complicated postoperative course. Currently their use is only on demand. The PRECious protocol presented here is a postoperative quality control algorithm, which is aimed at early diagnosis and treatment of patients with major complications.

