### Patient allocation and design

Patients will be informed about the study at the outpatient clinic. The patient will be included upon admission after informed consent has been obtained. Due to the nature of the study, a parallel-randomized design is not the preferred option, because this would allow for bias by crossover and automated CRP and CT enquiries by physicians in both patient groups. A cluster design is not deemed feasible due to differences between the participating centers (i.e., academic and teaching hospitals). A stepped-wedge design is deemed appropriate. Due to the large number of participating centers, little bias is expected from other changes in treatment. Changes will be monitored and corrected for if applicable. Thus, the two groups will be compared according to two periods. Patients allocated to the first period will receive standard on-demand additional examinations. After a transition phase of one month allowing for implementation, all patients will be allocated to the intervention arm and will receive standardized postoperative monitoring of serum CRP levels on POD 3, 4 and 5. If CRP levels exceed 140 mg/L additional CT will be conducted.

Data collection will be via an online module, which allows for inclusion and data collection. Participating surgeons will be able to log in to the secured module via the PRECious trial website. After completing the inclusion form, an immediate response with a code number and type of postoperative control protocol will be obtained.

The nature of the study does not allow for blinding, because it would not be ethical to perform sham venous puncture, and the protocol will be known by the attending physician to allow CT to be arranged. Instead of blinding, the add-on value of CRP measurements will be tested. The attending physician will have to grade the patient in the morning before CRP levels are known, grade 1 indicating a healthy patient, grade 10 a patient at acute risk of death. The physician will also have to state whether he/she would perform CT prior to CRP levels being measured, allowing for assessment of the add-on value of the presented standardized quality control algorithm.

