### Data collection and statistics

Data will be collected partially by means of a secured Internet module and partially by hard-copy datasheets. The secured online module is especially designed for the PRECious trial. Hard-copy datasheets, such as completed quality of life questionnaires will be sent to the VU medical center by mail, were they will be kept in a secured room. Data will be collected daily until discharge. PROMs will be collected preoperatively, and at 5 days, 3 months and 12 months postoperatively. A study chart for measurements is depicted in Table 1.

**Table 1 Tab1:** Study measurements

	Study period										
	Enrolment	Allocation	Post-allocation								Close-out
Time point	Pre-operative	Pre-operative	Surgery	POD 2	POD 3	POD 4	POD 5	Discharge	3 Mo	12 Mo	t_x_
Enrolment											
Eligibility screen	X										
Informed consent	X										
Allocation		X									
Interventions											
Control group		X									
CRP measurement				X	X	X	X				
QOL questionnaire		X					X		X	X	
PRECious group											
CRP measurement				X	X	X	X				
CT if CRP >140 mg/L					X	X	X				
QOL questionnaire		X					X		X		
Assessments											
Control group											
List baseline variables		X									
List operative data			X								
List admission data								X			
Quality of life		X					X		X	X	
List morbidity								X	X	X	
List survival								X	X	X	
PRECious group											
List baseline variables		X									
List operative data			X								
List admission data								X			
Quality of life		X					X		X	X	
List morbidity								X	X	X	
List survival								X	X	X	X

*POD* postoperative day, *Mo* months, *CRP* C-reactive protein, *CT* computed tomography scan, *QOL* Quality of Life, T_x_ end of protocol

One research fellow in the VU medical center will monitor the data for all included patients, and maintain regular contact with all participating centers. Due to the nature of the study the researcher cannot be blinded, hence an external monitoring committee (Clinical Research Bureau, Amsterdam, Netherlands) is installed and will assess data collection. All required parameters will be collected in an SPSS data file. Data analysis will be performed according to the intention-to-treat principle. Continuous variables will be compared using the *t* test or Mann-Whitney *U* test, as appropriate. Frequencies will be compared using the Chi-square or McNemar tests, as appropriate.

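### Table 1 schedules CRP on postoperative days 2 to 5 for control patients, while the text allows them blood sampling only on demand

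*Protocol article*

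**What the plan says.** **Text on control care.** Three places agree.

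- Abstract, Methods: "The first period consists of standard postoperative monitoring, which entails on demand additional examinations".
- Patient allocation and design: "Patients allocated to the first period will receive standard on-demand additional examinations".
- Standard group, which names blood sampling explicitly: "Additional examinations such as blood sampling and imaging will only be conducted on demand".

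**Table 1 (Data collection and statistics).** Under Interventions, the control group has a row labelled "CRP measurement" with marks at POD 2, 3, 4 and 5. The PRECious group has a row with the same label and the same four marks. The control row carries no qualifier, and the footnote only expands abbreviations. The control block has no CT row.

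**Text on the PRECious arm.** The PRECious group section sets routine CRP sampling on those four days as part of the PRECious protocol. The Economic evaluation books the additional testing to that arm: "These will include the increased costs in the PRECious arm due to the extra CRP testing and greater use of CT".

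**The concern.** A measurement fixed on four named days is not an on-demand measurement, so a site cannot follow both Table 1 and the Standard group section.

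Which rule applies matters because routine CRP is one of the two components of the intervention; the other is mandatory CT when CRP exceeds 140 mg/L on POD 3, 4 or 5. The trial is open-label. If controls were sampled as printed, and nothing says the results would be withheld, their physicians would hold the same CRP values on the same days and could order CT on demand in response. The contrast between the two periods would narrow, and the scheduled difference in CRP testing that the Economic evaluation counts would disappear.

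**Working it through.** **1. Reading of the table row.** Set against the header (two pre-operative columns, surgery, POD 2, 3, 4, 5, discharge, 3 months, 12 months, close-out), the control CRP row has its four marks under POD 2, 3, 4 and 5 and nowhere else. Label and marks are intact, so a fault in the PDF conversion is unlikely.

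**2. Group size used below.** Power of the study gives 525 per group for 17 % versus 11 %, two-sided alpha 0.05 and 80 % power. As a check, with pooled variance and no continuity correction:

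n = [z(0.975) × √(2 p̄ q̄) + z(0.80) × √(p₁q₁ + p₂q₂)]² / (p₁ − p₂)²

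With p̄ = 0.14:

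- first term: 1.960 × √0.2408 = 0.962
- second term: 0.842 × √(0.1411 + 0.0979) = 0.411
- n ≈ 1.373² / 0.06² ≈ 524 per group

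Power at 525 per group is 80.1 %. The stated size is reproduced and is not in dispute; it is used only to count samples.

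**3. Scheduled CRP samples on POD 2 to 5** (maximum, every patient sampled on all four days):

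| | Control | PRECious | Difference |
|---|---|---|---|
| Text | 0 × 525 = 0 | 4 × 525 = 2,100 | 2,100 |
| Table 1 | 4 × 525 = 2,100 | 4 × 525 = 2,100 | 0 |

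**4. Samples the row would add in practice.** Some controls would have CRP taken on demand anyway. The document does not say how often, so let k be the assumed number of such samples per control on POD 2 to 5. The row adds 525 × (4 − k):

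| k (assumed) | Samples added |
|---|---|
| 0 | 2,100 |
| 1 | 1,575 |
| 2 | 1,050 |
| 3 | 525 |
| 4 | 0 |

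**5. Which side is probably wrong.** The evidence for the text:

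- Patient allocation and design rejects a parallel-group trial because "this would allow for bias by crossover and automated CRP and CT enquiries by physicians in both patient groups". Routine control CRP would bring in the CRP half of what the design was chosen to avoid.
- The same section explains the lack of blinding by saying that "it would not be ethical to perform sham venous puncture". Had controls been bled on the same days, no sham puncture would be needed.
- The Economic evaluation counts more CRP testing in the PRECious arm. Under Table 1 there is no scheduled excess.
- The PRECious group section places routine sampling inside the PRECious protocol and has a transition period before measurements begin in that group.
- The Background says of CRP and CT: "Currently their use is only on demand". This describes general practice rather than the control arm, so it is weak support.
- Table 1 shows another slip: the PRECious quality-of-life row under Interventions lacks the 12-month mark that the Assessments block carries and the text requires.

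The evidence for intended observational sampling of controls:

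- The Discussion says changes in CRP from POD 2 to 5 will be compared, without naming an arm.
- The physician's grading before CRP is known, in Patient allocation and design, is also not tied to an arm.
- The control block has a CRP row but no CT row, which would fit CRP being measured without the CT rule.

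No section describes such sampling, says the results would be withheld, or says what to do with a control value above 140 mg/L.

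**The case against.** The strongest reply is that this is a one-row drafting slip in a journal article, which every prose statement on control care overrides. Sites work from the full protocol (version 2.0), which may not carry the row. The online module also returns the type of monitoring protocol when a patient is included, so staff are told which regimen applies. Even as printed, the table gives controls no CT rule, so the CT trigger remains specific to the PRECious arm. The sample count is simple multiplication, and its practical range runs down to zero. Finally, the direction of the error is not certain, Fig. 1 is not shown, and deleting the row would serve as well as relabelling it.

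Much of this stands as a limit on the harm. The harm is conditional, the missing CT row reduces it, and no effect on the endpoint, power or euros can be calculated. It does not remove the contradiction: the article states two different control conditions, and one of them sits in the measurement schedule. The module names the regimen, but that does not settle whether the control regimen includes scheduled CRP. In an open-label trial, visible CRP values can prompt CT without a formal trigger. Uncertainty about direction is a reason to ask the sponsor to settle it, since one side has to change on either reading.

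**Conclusion.** The point holds: Table 1 and the text contradict each other on whether control patients have scheduled CRP on POD 2 to 5. The size is 0 versus up to 2,100 scheduled control samples, so the scheduled between-arm difference is 2,100 or 0. The number actually added depends on on-demand use, which the document does not give.

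The contradiction itself is certain. That the table row is the wrong side is an inference from the rest of the text; planned observational sampling of controls is less likely but not excluded. Any damage to the contrast or to the cost comparison depends on sites following the row, and its effect on outcome or power is unknown. It should be fixed, because it concerns one component of the intervention and can be settled before any patient is enrolled: Trial status says recruitment has not begun.

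**What to change.** Before recruitment, relabel the control-group CRP row in Table 1 to say that CRP is recorded only if measured on demand; deleting the row would also resolve the conflict. Check that the full protocol and the site schedules agree.

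If routine control sampling is really intended, keep the row and instead correct the Abstract, Patient allocation and design, Standard group and Economic evaluation. In that case also state how control results will be handled: whether clinicians see them, and what follows a value above 140 mg/L.

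For the relabelling, the cost is one table row and one consistency check, with no extra data and no change to the sample size.

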#### PRECious group

The second period will be considered the intervention group. All patients will be allocated to postoperative controls according to the PRECious protocol. Within this protocol peripheral blood samples for CRP measurements will be collected routinely on POD 2, 3, 4 and 5. If CRP exceeds 140 mg/L on the third, fourth or fifth POD, enhanced CT of the abdomen will be conducted within 24 hours. It is expected that two thirds of patients will undergo CT versus one third of the control group. Intravenous contrast is administered, with regard to renal function, to conduct CT. Depending on the organ undergoing surgery, oral or rectal contrast will be administered, for which the patient will have to drink oral contrast or receive rectal administration prior to CT. After the first postoperative week, CRP samples will be collected on demand, according to the consulting physician. If a major complication is diagnosed, immediate treatment will be commenced as soon as possible and as appropriate. All major complications are to be confirmed in reoperation or suspicious drain fluid upon percutaneous drainage and culture.

To allow for correct implementation of the protocol a transition period of month is deemed necessary before starting measurements in the intervention group. A flow-chart depicting the design of the study is displayed in Fig. 1.

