### Endpoints

The primary endpoint of the study consists of a combined endpoint entailing all morbidity and mortality due to major complications. Complications will be classified according to a modified Clavien-Dindo classification in two groups [34, 35]. Group I consists of grade I and grade II complications, which are classified as minor. Early detection of major complications that may require invasive treatment, such as re-laparotomy or percutaneous drainage and/or intensive care admission, which might even lead to death, as classified by Clavien-Dindo grades III, IV and V, is of major importance. The comprehensive complication index will also be calculated [38]. All mortality and morbidity after major complications will be recorded, entailing fistula; bowel obstruction or herniation; abscesses; wound dehiscence; abdominal compartment syndrome; unplanned enterostomy; enterostomy dysfunction; myocardial infarction; pulmonary embolism; respiratory insufficiency; urosepsis; cerebrovascular accident; bleeding, and anastomotic leak.

Secondary endpoints will be patient-related outcome measures (PROMs), measured with the EuroQol-5D (EQ-5D) and gastrointestinal quality of life index (GIQLI) questionnaires. Furthermore postoperative recovery data will be collected in both groups, such as length of hospital stay and intensive care length of stay. Alongside the trial a cost-effectiveness analysis will be conducted.

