#### Postoperative management

Besides differences in postoperative controls, postoperative management will be similar in both groups. Early mobilization will be encouraged, starting with sitting out of bed the first day postoperatively. A dietician will monitor intake. Patients will be discharged when they pass stools, are able to drink and eat sufficiently and are comfortable with oral analgesia. Follow up will be scheduled at the outpatient clinic 3 and 12 months after the index operation. Here PROMs will be collected and morbidity monitored.

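### The requirement that all major complications be confirmed at reoperation or by drain fluid conflicts with the primary endpoint definition and stands only under the PRECious group, so its scope and arm need to be stated

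*Protocol article*

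**What the plan says.** **Endpoint.** The Endpoints section states: "The primary endpoint of the study consists of a combined endpoint entailing all morbidity and mortality due to major complications". It describes major complications as those for which an intervention may be needed: "such as re-laparotomy or percutaneous drainage and/or intensive care admission, which might even lead to death, as classified by Clavien-Dindo grades III, IV and V". The events to be recorded include "myocardial infarction; pulmonary embolism; respiratory insufficiency; urosepsis; cerebrovascular accident; bleeding, and anastomotic leak". Nothing in that section distinguishes the two groups.

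**Confirmation.** The only statement on how a major complication is confirmed is in the PRECious group section: "All major complications are to be confirmed in reoperation or suspicious drain fluid upon percutaneous drainage and culture". It follows the sentences on CRP, abdominal CT and prompt treatment.

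**Control period.** The Standard group section says "Additional examinations such as blood sampling and imaging will only be conducted on demand". It has no confirmation requirement, and none appears under Endpoints, Data collection and statistics, or Postoperative management.

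**Setting.** Patient allocation and design says "The nature of the study does not allow for blinding" and compares the groups as two periods. Postoperative management adds: "Besides differences in postoperative controls, postoperative management will be similar in both groups". That sentence is about care, not about how endpoint events are confirmed.

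**The concern.** There are two problems, and the first does not depend on the second.

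1. **The sections do not fit together.** One section makes a set of events major by grade. Another says that every major complication is confirmed by a route open to only some of them. A centre cannot follow both to the letter for a stroke, an infarction or a death without re-intervention.

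2. **The placement matters.** If the sentence is taken as an endpoint rule and as applying only where it is printed, a non-surgical event would count on its grade in the first period and fail confirmation in the second. Treatment and period go together in this comparison, so the analysis could not separate such a difference in counting from a treatment effect. It would favour the intervention, and staff know which period they are in.

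What is at stake is which events enter the primary endpoint and whether the answer is the same in both periods.

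**Working it through.** **Step 1. Set the definition against the confirmation route.**

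| Event that Endpoints treats as major or lists | Can reoperation, or drain fluid with culture, confirm it? |
|---|---|
| Re-laparotomy, percutaneous drainage, anastomotic leak, abscess | Yes, when re-intervention takes place |
| Myocardial infarction, pulmonary embolism, respiratory insufficiency, cerebrovascular accident | No |
| Urosepsis | Poor fit |
| Intensive care admission without re-intervention | No |
| Death without re-intervention | No |

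The conflict between the two sections is therefore established without any assumption about groups.

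**Step 2. List the readings that the text leaves open.**

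- *A. Clinical pathway only:* the sentence describes how CT findings are verified, and counting follows Endpoints. The count is unaffected, and the fault is one of wording.
- *B. Endpoint rule in both periods:* non-surgical events are lost from both groups. The rule is then the same for both, but events and power are lost.
- *C. Endpoint rule in the PRECious period only:* non-surgical events are lost from one group.

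**Step 3. Reproduce the planned sample size.** The inputs, all from Power of the study, are 17% v 11%, two-sided 0.05, 80% power and 525 per group. With the pooled variance under the null,

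n = [1.960 √(2 × 0.14 × 0.86) + 0.842 √(0.17 × 0.83 + 0.11 × 0.89)]² / 0.06² = 524 per group.

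Power at 525 is 80.1%. The stated figure reproduces and is not disputed.

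**Step 4. Illustrate reading C.** Assume a true rate of 17% in both groups, all control events counted, and an apparent PRECious rate q. The share of events lost is an assumption, because the documents do not give it. The calculation uses the normal approximation with no allowance for centre. With d = 0.17 − q and p̄ the mean of 0.17 and q,

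P(significant) = Φ[(d − 1.96 s₀)/s₁] + Φ[(−d − 1.96 s₀)/s₁],

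where s₀ = √(2p̄(1 − p̄)/525) and s₁ = √((0.17 × 0.83 + q(1 − q))/525).

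For q = 0.15, d = 0.02 and s₀ ≈ s₁ ≈ 0.0226. The first term is Φ(−1.08) = 0.141 and the second is 0.002, in total 0.143.

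| Assumed loss from the PRECious group | Apparent rates | Chance of p < 0.05 with no true effect |
|---|---|---|
| None | 17% v 17% | 5.0% |
| 5% of events | 17% v 16.15% | 6.6% |
| 2 points (2/17 = 11.8% of events) | 17% v 15% | 14.3% |
| 3 points (3/17 = 17.6% of events) | 17% v 14% | 26.9% |

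**Step 5. Illustrate reading B.** Assume the same share is lost from both planned rates. A 10% loss gives 15.3% v 9.9% and power of 75%. A 20% loss gives 13.6% v 8.8% and power of 69%.

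**Step 6. Ask how large the share could be.** Power of the study describes the 17% by multiple reoperations, multiple percutaneous drainages and enterostomy at re-intervention. All three are surgical or interventional, so the route could confirm them. Mortality is also within the 17%, and the number of deaths without re-intervention is not given. On that description the share may be near the top of the Step 4 table. The Endpoints section does not limit the endpoint to those components, so the share cannot be fixed from the documents.

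**The case against.** The strongest reply is that the sentence belongs to a clinical sequence: raised CRP, abdominal CT, diagnosis, treatment, then verification. Read so, it is a reference standard for what CT finds and not a counting rule. Counting is set elsewhere and equally for both groups. Endpoints grades by Clavien-Dindo without naming a group. Table 1 lists morbidity and survival at discharge, 3 months and 12 months for both. Postoperative management schedules the same follow-up visits for both. The sentence itself says all and carries no arm qualifier; only the heading above it restricts it. This is also a condensed article, and event-specific criteria may well stand in the full protocol.

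Much of this stands. A reader might infer that the protocol builds in a bias toward the intervention, with strokes and deaths counted in the control period and discarded in the PRECious period. The documents do not support that. It needs three things that are not stated: that the sentence governs counting, that it binds one group only, and that an unconfirmed event is excluded. A reader might equally take 14% or 27% as the false-positive rate of this trial. Those figures rest on 2 or 3 of the 17 points being unconfirmable, and the components named for the 17% give that no support.

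Two things survive. The sentence is in the text and, as worded, cannot be met by events that Endpoints counts; this is a stated conflict and not an omitted detail. And no other passage says which of the three readings is meant.

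**Conclusion.** The conflict between the Endpoints and PRECious group sections is real and needs no assumption. That counting could differ by period is a possibility left open by the placement of the sentence, in an open-label trial compared by period; it is not shown to happen. If it did, the direction would favour the intervention.

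The size is unknown. It ranges from no effect, if the sentence is a clinical verification step, to the values illustrated above, which require an assumed share of events that cannot be confirmed this way. The surgical description of the 17% suggests that the share may be small. The sample size itself is sound on its stated inputs. The point is worth settling because it decides what counts as a primary endpoint event, and because events left unconfirmed may be hard to recover later.

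**What to change.** Reconcile the Endpoints, Power of the study and PRECious group sections:

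- State one endpoint-confirmation standard in Endpoints, and say that it applies identically in both periods.
- Limit confirmation by reoperation or drain fluid to the intra-abdominal complications it can confirm.
- State that non-surgical major complications, intensive care admissions and deaths count by their Clavien-Dindo grade in both periods.
- Say whether the 17% in Power of the study measures the endpoint as Endpoints defines it or only the surgical components named there.
- If the sentence in the PRECious group section is meant only as verification of CT findings, say so there and state that it does not decide endpoint counting.

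The cost is about one paragraph of wording. The Trial status section says that recruitment had not begun, so no data would need to be reclassified. Neither the sample size nor patient management changes.
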